## Background

### Scientific background and explanation of rationale

Postoperative nausea and vomiting (PONV) is a common and distressing problem that affects 20-30% of surgical patients after general anesthesia [1]. PONV not only reduces patient comfort but can also lead to serious postsurgical complications, such as dehydration, electrolyte imbalances, the aspiration of the gastric contents, esophageal rupture, suture dehiscence and bleeding [2-9]. Furthermore, PONV significantly affects healthcare costs by prolonging hospital stays [10,11]. In particular, patients undergoing thyroidectomy exhibit a high incidence of PONV, which can be as high as 80% [2,12,13]. PONV after thyroidectomy is most likely caused by edema and inflammation around the neck tissues, leading to evoked parasympathetic impulses through the vagus, recurrent laryngeal and glossopharyngeal nerves to the vomiting center [13-15].

Dexamethasone, a glucocorticosteroid, has been described as highly effective against chemotherapy-induced nausea and vomiting [16,17]. A recently published study comparing the efficacy of six well-established antiemetic strategies concluded that the use of dexamethasone as a first-line method of prophylaxis for PONV is a reasonable treatment option [18]. The exact mechanism by which dexamethasone exerts its antiemetic activity is not well understood. The antagonizing effect of corticosteroids on inflammatory reactions and the dexamethasone-triggered release of endorphins, which results in mood elevation, a sense of well-being and appetite stimulation, may contribute to this effect [19-21]. Due to their anti-inflammatory activity, corticosteroids have been shown to reduce postoperative swelling, pain and sore throat [22-25]. Despite these advantages, the perioperative use of dexamethasone for the prophylaxis and treatment of PONV has not been established [26], possibly due to concerns that the use of corticosteroids would increase susceptibility to infections. However, several studies have indicated that even long-term corticosteroids treatments do not lead to a significant increase in wound infections [27-29]. Another possible reason is the lack of awareness about the antiemetic effect of this type of medication.

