### Outcome measurements

The primary outcome will be the incidence of PONV, which will be assessed at postoperative hours 4, 8, 16, 24, 32 and 48. A patient will be considered to suffer from PONV if nausea or vomiting is documented at any of the postoperative assessments.

One secondary outcome will be the severity of the PONV, measured with a score ranging from 0 to 3 (0 for no nausea; 1 for mild nausea, defined as nausea requiring a single administration of an antiemetic drug; 2 for severe nausea, defined as nausea requiring the repeated administration of antiemetic drugs; and 3 for nausea leading to vomiting).

Other secondary outcomes will be the intensity of pain at rest and under provocation (while rotating the neck 90° to each side), measured at postoperative hours 4, 8, 16, 24, 32 and 48 with a Verbal Rating Scale (VRS) ranging from 0 to 10, with 0 considered to be no pain and 10 considered to be the worst pain imaginable. Additional secondary outcomes will include the length of hospital stay (measured as the number of hours after the intervention), wound healing at the time of discharge and six weeks after the intervention, the amount of anesthetic medication required (total amount of administered fentanyl, remifentanil, rocuronium measured in mg and the total amount of administered remifentanil measured in μg) and postoperative in-hospital morbidity, including wound infection, reoperation, bleeding, prolonged intubation, laryngeal nerve lesion, urinary retention, urinary tract infection, pulmonary infection and gastrointestinal hemorrhage or newly occurring insulin dependence in diabetic patients.

For the safety analysis, adverse events (AEs) and serious adverse events (SAEs) will be evaluated. The patients will be instructed by the investigator to report the occurrence of any AE, defined as an unfavorable and unintended sign, symptom or disease temporally associated with the treatment provided in the present trial. The investigator (treating physician) will be asked to verify the absence or presence of all the AEs predefined on the CRF. Information in the patients’ medical files will be reported using the Common Terminology Criteria for Adverse Events v4.03 (CTCAE 4.03) coding system, rather than a narrative description. AEs will be scored as grade 1 (a mild AE) to grade 5 (death related to the AE), and a causality assessment will be performed.

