All grade 4 or 5 AEs will be counted as SAEs, with the exclusion of PONV (as the primary outcome), delayed wound healing (as a secondary outcome) and wound infection (as a secondary outcome). Additionally, postoperative hypoparathyroidism and lesions to the recurrent nerve will not be counted as SAEs because they are considered imminent risks of a thyroidectomy.

The local Ethics Committee and Swissmedic will be informed by the principal investigator about SAEs according to local legislation (VKlin/HMG). A yearly safety summary will be provided to the local Ethics Committee and Swissmedic.

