### Statistical analysis

The statistical analysis will be performed with SAS 9.1 (SAS Institute Inc., Cary, NC, USA). Missing values will be replaced with the last available value (the last observation carried forward approach, LOCF). For the baseline characteristics, descriptive statistics will be used as appropriate.

Two analyses (interims analysis and final analysis) will be performed for the primary outcome. To maintain the alpha, an O’Brien-Flemming alpha spending function [40] will be used. The alpha values used for the primary outcome will be 0.0039 in the interim analysis and 0.0488 in the final analysis. Both alphas will be adjusted for the exact proportion of information included in the interim analysis if the analysis is not performed for exactly 70 patients. For all other analyses, two-sided significance tests with an alpha of 0.05 will be applied.

All confirmatory analyses will be performed primarily as ITT analyses; the available data from all the patients will be assessed for the outcomes according to the randomization. To assess the treatment effects of dexamethasone vs. placebo in patients with no postoperative use of opioids, additional analyses will be conducted excluding the patients with protocol violations.

For the superiority analysis of dexamethasone vs. placebo in terms of the incidence of PONV (the primary outcome), a chi-square statistic will be applied. Mixed models assessing the mean ranks of the scores with adjustments for time and treatment vs. time interactions will be applied to analyze the following secondary outcomes: the severity of PONV, the intensity of pain at rest and the intensity of pain under provocation. The Mann–Whitney U statistic will be used to assess the following secondary outcomes: the required amount of anesthetic medication, the amount and type of postoperatively administered analgesics and the length of hospital stay. Postoperative morbidity and wound healing at the time of discharge and six weeks after the intervention will be assessed using a chi-square statistic.

Auxiliary, non-confirmatory analyses will be performed to assess the influences of baseline and treatment characteristics on the primary and secondary outcomes.

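### PONV is exempt from SAE counting at every grade because it is the primary outcome, but neither PONV outcome records grade 4–5 severity; only the general AE grading does.

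*Protocol article*

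**What the plan says.** The rule stands in the Outcome measurements section of the protocol article: "All grade 4 or 5 AEs will be counted as SAEs, with the exclusion of PONV (as the primary outcome". Delayed wound healing and wound infection are exempt on the same footing, as secondary outcomes. No upper grade limits the PONV exemption.

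The same section defines the primary outcome: "A patient will be considered to suffer from PONV if nausea or vomiting is documented at any of the postoperative assessments". The Statistical analysis section then specifies: "For the superiority analysis of dexamethasone vs. placebo in terms of the incidence of PONV (the primary outcome), a chi-square statistic will be applied". The secondary severity score runs from 0 to 3. Its levels 1 and 2 depend on how often antiemetics were given, and its highest level is "3 for nausea leading to vomiting".

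Adverse event (AE) recording is separate from both: "For the safety analysis, adverse events (AEs) and serious adverse events (SAEs) will be evaluated". Events are coded in CTCAE 4.03 with a causality assessment, and "AEs will be scored as grade 1 (a mild AE) to grade 5 (death related to the AE".

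SAE status is used in two places. The principal investigator informs the Ethics Committee and Swissmedic about SAEs (Outcome measurements). At the interim analysis the chairperson and co-chairperson decide on the trial's continuation from SAE summary tables and an analysis of the primary outcome (Interim analysis).

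**The concern.** Exempting an outcome event from SAE reporting is usually justified on two grounds: the event is so common that reporting it would swamp the system, and it is already captured in full as an outcome. Neither ground holds here. Common PONV is below grade 4 and would not be an SAE anyway, and the outcome measures do not capture seriousness.

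The protocol itself treats PONV as potentially grave. The Background says that it "can also lead to serious postsurgical complications, such as dehydration, electrolyte imbalances, the aspiration of the gastric contents, esophageal rupture, suture dehiscence and bleeding". One arm receives saline only, and planning assumes a 48% incidence of PONV without the drug. A difference between arms in the very worst PONV is something an SAE comparison should be able to show. As written, such events would not appear in it.

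**Working it through.** No arithmetic applies, because the plan gives no figure for grade 4–5 PONV. The check is to set the rules side by side and follow one event through them.

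**Which grades the exemption acts on.** Under Outcome measurements an AE becomes an SAE only at grade 4 or 5. PONV of grades 1–3 is outside the SAE count with or without the exemption. The rule therefore changes the status of grade 4 and 5 PONV only. The article spells out only grade 1 (mild) and grade 5 (death); grade 4 is taken here in its usual sense of life-threatening.

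**What each record shows.**

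| Record | Vomiting, grade 1–3 | Event coded only as PONV, grade 4–5 |
|---|---|---|
| Primary outcome | yes | yes |
| Severity score 0–3 | 3 | at most 3 |
| CTCAE grade in the AE data | 1–3 | 4 or 5 |
| SAE count | no | no, by exemption |
| SAE notification to Ethics Committee and Swissmedic | no | no |
| Interim SAE table | not shown | not shown |

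The primary outcome and the severity score cannot separate the two columns. The CTCAE row can. The last three rows are where any other grade 4–5 event off the exemption list would differ from a mild one, and where PONV does not.

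**Whether the stated reason fills the gap.** The reason given is that PONV is the primary outcome. That outcome is binary and is compared by incidence, so a fatal event adds one yes, the same as brief nausea. The Discussion describes PONV more narrowly, as vomiting or receipt of antiemetic medication, but that version is also yes/no. The score stops at "3 for nausea leading to vomiting" and has no level above it. Neither measure stands in for the SAE count.

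**A related inconsistency.** The Interim analysis section speaks of tables of grade 3 and 4 SAEs, while Outcome measurements defines SAEs as grade 4 or 5. Read literally, grade 5 appears in no interim SAE table for any event, so the exemption affects that table through grade 4. The two passages need reconciling in their own right.

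**The case against.** The strongest reply is that nothing is lost from the trial data. AEs as well as SAEs enter the safety analysis, AEs are graded 1 to 5 with causality, and PONV is removed from the SAE count only. That stands. A reader might infer that a grade 4–5 event would look like any other vomiting throughout the trial; the article does not support this. It is true of the two PONV outcomes but not of the AE data. How PONV is entered on the predefined AE list of the case report form is not shown in this condensed article, so nothing can be concluded about how well its grade is captured.

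A reader might also infer that the grave consequences named in the Background have been taken out of SAE reporting. They have not. Aspiration, esophageal rupture and bleeding are not on the exemption list and count as SAEs at grade 4 or 5 when coded under their own term; suture dehiscence could arguably be coded as delayed wound healing, which is exempt. Several sequelae, such as bleeding and pulmonary infection, are also recorded as in-hospital morbidity and compared by arm.

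It would likewise be wrong to size the gap by the planning incidences of 48% and 24%. Those count PONV of any grade, and the rule bears only on grades 4 and 5.

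Finally, the exemption is openly stated, two secondary outcomes are treated alike, rescue antiemetics are provided, the Ethics Committee and Swissmedic approved the protocol, and an excess of PONV in one arm would be visible in the interim analysis of the primary outcome. All of this is fair and makes the point smaller. None of it restores SAE status under the written rule, and the interim primary outcome shows frequency, not grade.

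**Conclusion.** The point holds in a limited form. The exemption has one effect, which is to take grade 4–5 PONV out of the SAE count, the SAE-based notification and the interim SAE table, and the reason given for it fails against the protocol's own outcome definitions. What remains exposed is an event coded solely as PONV at grade 4 or 5, with no separately coded complication. The general AE grading is the only record of its severity.

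The size in numbers cannot be stated. The article gives no rate, and such events are presumably very rare. No efficacy result, sample size or alpha is affected. The conclusion assumes that the SAE definition under Outcome measurements governs, and that local legislation or the yearly safety summary, whose content is not described, does not override the written exemption. It concerns an explicit rule with an unsound reason, not detail left to a fuller document.

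**What to change.** In the SAE paragraph of Outcome measurements, do one of two things:

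- delete PONV from the list of exemptions; or
- state that PONV of grade 4 or 5 is counted and reported as an SAE and shown by arm in the SAE tables, with coded arms at the interim analysis.

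Both leave PONV of grades 1–3 where it is now and leave PONV unchanged as the efficacy outcome. No clause on complications is needed, since those coded under a non-exempt term already count. While the paragraph is open, its SAE grades should be reconciled with those named in the Interim analysis section.

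The cost is one sentence in the protocol and matching guidance for the case report form. The only downside is a possible few extra SAE reports.

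### Hypoparathyroidism and recurrent nerve lesions are exempt from SAE status at any grade, so grade 4–5 cases drop out of SAE notification and the interim safety tables

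*Protocol article*

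**What the plan says.** All references are to the protocol article.

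- **SAE definition (Outcome measurements).** "All grade 4 or 5 AEs will be counted as SAEs, with the exclusion of PONV (as the primary outcome"; delayed wound healing and wound infection are also excluded, because each is a secondary outcome.
- **Further exemption (same section).** "postoperative hypoparathyroidism and lesions to the recurrent nerve will not be counted as SAEs because they are considered imminent risks of a thyroidectomy". No grade is mentioned.
- **Notification (same section).** The principal investigator informs the Ethics Committee and Swissmedic of SAEs as local law requires. A yearly safety summary is also sent; its content is not described.
- **Morbidity outcome (same section).** The list reads "postoperative in-hospital morbidity, including wound infection, reoperation, bleeding, prolonged intubation, laryngeal nerve lesion, urinary retention" and continues with other items. It names laryngeal nerve lesion. It names neither hypoparathyroidism nor low calcium.
- **Test of morbidity (Statistical analysis).** "Postoperative morbidity and wound healing at the time of discharge and six weeks after the intervention will be assessed using a chi-square statistic".
- **General AE capture (Outcome measurements).** "For the safety analysis, adverse events (AEs) and serious adverse events (SAEs) will be evaluated", and "AEs will be scored as grade 1 (a mild AE) to grade 5 (death related to the AE), and a causality assessment will be performed".
- **Interim analysis.** After 70 patients the statistician supplies tables of SAEs of grades 3 and 4, together with an analysis of the primary outcome by coded arm. The chairperson and co-chairperson decide from these whether to continue, modify or halt the trial.

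**The concern.** Seriousness and expectedness are different properties. The section sets seriousness by grade and then waives it for two diagnoses because the operation is known to cause them. That a complication is a known surgical risk does not show that the study drug leaves its frequency or severity unchanged. In a placebo-controlled randomised trial the control arm carries the surgical background risk, and the comparison between arms shows whether the drug alters it. The other three exclusions have a different justification: each event is already an outcome. That reason is not offered here, and for hypoparathyroidism it could not be, since it is not a named outcome.

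At stake is whether the worst cases of two complications that the protocol itself regards as typical of the operation reach the people meant to act on serious events: the authorities, through notification, and the chairpersons at the interim.

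**Working it through.** No figure in the plan bears on this point, so the check is a reading of the rules side by side.

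**Step 1: which cases the exemption removes.** SAEs are AEs of grade 4 or 5. The exemption covers the two diagnoses at all grades, 1 to 5. The overlap is grades 4 and 5. Grades 1 to 3 were never SAEs under this definition, so the exemption does nothing there; its whole effect is on grades 4 and 5. Grade 5 is defined as death related to the AE, so as written even a fatal case coded this way is not an SAE.

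**Step 2: where a grade 4–5 case still appears.**

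| Route | Recurrent nerve lesion | Hypoparathyroidism |
|---|---|---|
| Individual SAE notification (Outcome measurements) | absent | absent |
| Interim safety tables (Interim analysis) | absent | absent |
| Named morbidity item, chi-square by arm (Outcome measurements; Statistical analysis) | present | not named |
| Graded AE with causality assessment (Outcome measurements) | present | present |
| Yearly safety summary (Outcome measurements) | content not stated | content not stated |

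The two conditions therefore differ. Both lose the first two routes. Only hypoparathyroidism also lacks a named outcome comparison. Morbidity outcomes are not part of the stated interim package, so the nerve lesion comparison does not fill the interim gap.

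**Step 3: do the two SAE definitions agree?** Outcome measurements gives grades 4 and 5; Interim analysis tabulates SAEs of grades 3 and 4. They share only grade 4. A grade 3 event cannot be an SAE under the first rule, and a grade 5 event is an SAE under the first rule but is not in the tables described by the second. Removing the exemption alone would therefore still leave a fatal case outside the interim tables as described.

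**Step 4: likely size.** The protocol gives no rates. Purely as an assumption, take a combined grade 4–5 rate of 0.5% to 2%:

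- full trial: 152 × 0.005 = 0.76 to 152 × 0.02 = 3.04 events, both arms together;
- interim: 70 × 0.005 = 0.35 to 70 × 0.02 = 1.4 events.

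On that range the rule affects roughly one to three cases overall and none or one at the interim.

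**The case against.** The strongest reply has five parts.

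1. *The events are not lost.* This stands. Every AE is graded, assessed for causality and evaluated in the safety analysis, and nerve lesion is a named outcome. A reader might infer that life-threatening cases of both conditions go uncompared, or that any imbalance in hypoparathyroidism would go untested. The document supports neither: nerve lesion is tested by chi-square, and how AEs are tabulated by arm is commonly left to the analysis plan, which is not shown.
2. *The morbidity list is open-ended and the case report form is not shown.* This stands in part. The list is introduced as inclusive, and the predefined AEs on the form may cover hypoparathyroidism. It does not answer the SAE exemption, which is a stated rule and not an omitted detail.
3. *The exemption names diagnoses, not consequences.* This stands. Nothing exempts airway compromise or low calcium coded as its own grade 4 or 5 AE. The point is limited to cases coded as the two diagnoses.
4. *The Ethics Committee and Swissmedic approved the protocol, and they are the bodies that receive the reports.* True, but approval does not turn a reason of expectedness into one of seriousness, and it does not supply the missing cases to the interim review.
5. *The events would be too few to interpret.* This is probably right for a formal test. Individual notification and interim listing do not depend on a test; they exist so that single grave events are seen.

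A further tempting argument is that the background section makes a steroid effect on these complications plausible, because it describes inflammation "leading to evoked parasympathetic impulses through the vagus, recurrent laryngeal and glossopharyngeal nerves to the vomiting center". That text explains vomiting. It says nothing about nerve injury or parathyroid function, and the point does not rest on it.

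**Conclusion.** The concern holds in a limited form. As written, grade 4–5 cases coded as postoperative hypoparathyroidism or recurrent nerve lesion are not SAEs, and so are absent from individual SAE notification and from the safety tables used for the interim decision. For nerve lesion that is the whole gap. For hypoparathyroidism there is the further weakness that no outcome list in this document names it; it is captured only as a graded AE.

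The number of cases is unknown and probably small. The range in the working is an assumption, not a figure from the protocol. The conclusion assumes that the SAE definition is applied literally and that severe cases are coded under these two diagnoses rather than by their consequences. The primary outcome, its alpha levels and the sample size are not touched. It is worth correcting because the rule is explicit, its stated reason does not support it, and the change is cheap.

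**What to change.** - **Outcome measurements, SAE definition.** Remove the exemption for grade 4–5 cases of the two conditions. Confining it to grades 1–3 would amount to the same thing, since those grades are not SAEs under the definition, so plain deletion is clearer. If the sponsor keeps the exemption for notification, then at minimum tabulate grade 4–5 cases of both conditions by coded arm (A, B) in the interim safety tables.
- **Outcome measurements, morbidity list.** Name postoperative hypoparathyroidism beside laryngeal nerve lesion and report it by arm. With few events this comparison should be treated as descriptive.
- **Outcome measurements and Interim analysis.** Reconcile the SAE grades (4–5 in one, 3–4 in the other) and make clear that grade 5 events are included in the interim tables.

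The cost is a few sentences of wording, at most one item on the case report form if it is not already there, and probably a few extra SAE reports.
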